#### Sample Size

##### Objective 1

With the prevalence of dyspnea (MRC score: 2 out of 5) in 50% of the patients with hEDS and G-HSD, we estimate that 75% of the patients with hEDS will report a Borg dyspnea score of ≥4 (moderate dyspnea) compared with 25% of healthy controls after cardiopulmonary exercise, as previously observed at our center [74]. Thus, with a sample size of 34 patients with hEDS or G-HSD and 17 healthy controls, we will have 90% power to observe a significant difference in moderate dyspnea (α level=.05). Furthermore, given an estimate of 10 participants for each covariate in multivariable regression modeling, we reckon that enrollment of 34 participants with hEDS or G-HSD will allow us to explore at least 3 determinants of dyspnea in our models.

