**Secondary outcomes**						
	**Pulmonary function**					
		Spirometry and lung volumes	FEV1^b^ (L), FVC^c^ (L), TLC^d^ (L), RV/TLC^e^ (%)		Baseline (T_0_) and 8 weeks (T_2_)	
		Oscillometry	Oscillometry: respiratory impedance, reactance, and resistance		Baseline (T_0_) and 8 weeks (T_2_)	
		Respiratory muscle endurance time	Time (seconds) using the Philips Threshold trainer at 30% of baseline MIP		Baseline (T_0_), 4 weeks (T_1_), and 8 weeks (T_2_)	
		Diaphragm structure and function	Diaphragm thickness and thickening fraction		Baseline (T_0_) and 8 weeks (T_2_)	

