### Statistical Analysis

#### Proposed Data Analyses

For objective 1, we aim to compare respiratory muscle structure and function and PROMs between patients with hEDS or G-HSD and healthy controls and to evaluate the main correlates with dyspnea in patients with hEDS or G-HSD. Descriptive statistics will be used for continuous variables (mean and SD or median and IQR), and frequencies will be used for categorical variables. We will use multivariable regression analysis to compare any differences between groups across respiratory parameters and PROMs, adjusted for EDS subtype (hEDS or G-HSD). We will explore the associations with peak Borg dyspnea scores during CPET using multivariable regression, with possible determinants being MIP, diaphragm thickening fraction, PFC activity, and PFT parameters.

For objective 2, we aim to assess the feasibility of IMT and standard-of-care rehabilitation for improving respiratory muscle strength, exercise capacity, and PROMs compared with standard-of-care rehabilitation alone in patients with hEDS or G-HSD. Descriptive statistics will be used to summarize program adherence, recruitment, participant satisfaction, attrition, and safety in the hEDS or G-HSD study groups. Estimates of within- and between-group differences at T_0_, 4 weeks, and 8 weeks will be reported using means and 95% CI. Paired *t* tests and *t* tests will be used to compare the changes in the primary pilot outcome (MIP) and secondary measures over the 8-week study period within and between the 2 randomized groups.

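### With 34 patients, the protocol's own rule of 10 participants per covariate caps the dyspnea model at 3 covariates; the text states 3 as a minimum and lists four candidates

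*Protocol article*

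**What the plan says.** The protocol article makes identifying what contributes to dyspnea in hEDS or G-HSD part of its first aim (Study Aims). Under Proposed Data Analyses, objective 1 includes the intention "to evaluate the main correlates with dyspnea in patients with hEDS or G-HSD". The method is given as "We will explore the associations with peak Borg dyspnea scores during CPET using multivariable regression". The same sentence goes on to name the candidate terms: "with possible determinants being MIP, diaphragm thickening fraction, PFC activity, and PFT parameters".

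Under Sample Size, Objective 1, the capacity of that regression is justified by a rule of thumb, "given an estimate of 10 participants for each covariate in multivariable regression modeling". From this the article concludes that "enrollment of 34 participants with hEDS or G-HSD will allow us to explore at least 3 determinants of dyspnea in our models".

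The Data Management and Quality Assurance section adds that missing data will not be imputed and that analysis will use what is available.

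**The concern.** A participants-per-covariate rule limits how many terms a model may carry. Dividing the sample by the rule gives a maximum, but the article states the result as a minimum, which leaves the number of terms open in the direction the rule is meant to close. The analysis section then lists more candidates than the rule allows in one model.

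At stake is how far the contributors named at the end can be trusted. If four or more terms are fitted together in 34 patients, the analysis falls below the standard that the authors set for themselves. Coefficients become less precise, and apparent explanatory power rises through fitting noise. A reader of the results could also cite the sample size section as having allowed for it.

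**Working it through.** **Inputs, all from the protocol article**
- Patients in the model: 34. Both sections confine this analysis to hEDS or G-HSD patients.
- Rule: 10 participants per covariate (Sample Size, Objective 1).
- Outcome: peak Borg score during CPET, analysed as a score, so the rule counts participants and not events.
- Candidates: four entries, namely MIP, diaphragm thickening fraction, PFC activity and PFT parameters (Proposed Data Analyses).
- Missing data: no imputation (Data Management and Quality Assurance).

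No term for age, sex or EDS subtype is added here, because the article lists none for this model.

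**Reproducing the stated figure**

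Maximum covariates = whole part of n/10 = whole part of 34/10 = whole part of 3.4 = 3. The figure 3 reproduces, but as an upper bound. Three covariates give 34/3 = 11.3 patients each, which meets the rule.

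**The fourth covariate**

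Patients needed for k covariates = 10 × k. For k = 4 this is 40, which exceeds 34. At 34 patients, four covariates give 34/4 = 8.5 each, below 10. This is the most favourable count of the listed entries, since it treats PFT parameters as a single variable although the article uses the plural.

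**Incomplete data**

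Without imputation, a patient who lacks any term drops out of a multivariable model containing it. With 30 complete cases the limit is still 3. With 29 it is the whole part of 2.9 = 2. The limit therefore falls to two once five of the 34 lack a needed value (34 − 5 = 29).

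**Could the controls raise the limit?**

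Adding the 17 healthy controls would give 51/10 = 5.1, so five covariates. That is not available, because the article restricts both the model and the capacity statement to patients.

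**The case against.** The strongest reply is that the sentence speaks of models in the plural. The rule limits covariates per model, so three per model and three or more determinants across several models can both be true. The rule is also offered as an estimate, the candidates are called possible, and the verb is explore. On this view there is no arithmetic error, only loose wording, and the choice of terms belongs in a statistical analysis plan that is not shown.

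Much of this stands. The article does not commit to fitting every candidate together, and leaving the final choice of terms to an analysis plan is normal. The plural does not rescue the sentence, however. If the number of determinants is counted across any number of models, 34 patients at 10 per covariate sets no limit on it, and the figure 3 would not follow from the rule. The 3 comes from 34/10, which is a per-model quantity, and as such it is a ceiling. The point is thus a bound stated the wrong way round beside a list that exceeds it, and does not depend on missing detail.

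A reader might go further and expand PFT parameters using Table 3: four spirometry and lung volume measures plus the oscillometry entry "Oscillometry: respiratory impedance, reactance, and resistance". With MIP, thickening fraction and PFC activity that makes 3 + 4 + 3 = 10 candidates, or 34/10 = 3.4 patients each. If all ten entered one model and none mattered, the expected R-squared would be 10/(34 − 1) = 0.30, against 3/33 = 0.09 for three. Ten independent tests at 0.05 would carry a 1 − 0.95^10 = 40% chance of at least one false determinant.

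The documents do not support that reading. They do not say that every Table 3 pulmonary measure is a candidate, or that all enter one model, and they mention no stepwise or other automated selection. The count depends on what is treated as a PFT parameter. The 40% also assumes independence, which is implausible for related measures: the Oscillometry section itself describes impedance as composed of resistance and reactance. These figures illustrate one extreme and are not estimates for the planned analysis.

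**Conclusion.** The point holds in a limited form. On the article's own rule, 34 patients allow at most three covariates per model, so presenting three as a minimum is wrong for any single model. The list of possible determinants has at least four entries, one more than the rule permits together, which leaves 8.5 patients per covariate against the stated 10. Incomplete data could lower the limit to two.

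This rests on taking the stated rule at face value and on counting complete cases within each model. It makes no claim that 10 per covariate is the right standard.

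The consequence is modest. The analysis is exploratory and does not touch the primary pilot outcome. It is also separate from the 75% versus 25% comparison of moderate dyspnea that supports 34 patients and 17 controls. It still merits correction, because finding what contributes to dyspnea is a stated aim and the sample size text appears to license more terms than its rule supports.

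**What to change.** 1. In Sample Size, Objective 1, restate the capacity as up to 3 covariates per model, and note that it falls to 2 if fewer than 30 patients have complete data for the terms concerned.
2. Before the dyspnea data are examined, fix which three terms enter the main model for peak Borg dyspnea. If PFT parameters are represented, name the single measure used. The choice is for the investigators and can be recorded in the analysis plan.
3. Report the remaining candidates as exploratory single-predictor associations with confidence intervals, labelled as such.

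The cost is a change of wording and an early decision on three terms. No patients, visits or measurements are added. The downside is that fewer determinants can be claimed from the main model, and the associations reported outside it will be unadjusted for the others.

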##### Objective 2 (Primary Pilot Outcome)

Given an estimated MIP comparable with that of moderate COPD patients (mean 51, SD 15 cm H_2_O), we anticipate a mean increase of 10 (SD 3.5) cm H_2_O in MIP in the IMT and exercise training group compared with the hEDS or G-HSD usual care group (exercise training alone; 5 cm H_2_O) [75]. Assuming a maximum attrition rate of 20% among the 34 RCT participants with hEDS or G-HSD, we will have 90% power (α=.05) to observe a significant difference in MIP with 17 participants per group.

#### Data Management and Quality Assurance

Our research team is trained in the measurement protocols and has expertise in performing physical assessments and PROMs in individuals with respiratory conditions. The research team has critically appraised the peer-review comments from the 2020 GoodHope Ehlers-Danlos Syndrome foundation grant (Multimedia Appendix 1) and has incorporated them into the study protocol. Most of the study assessments will be conducted at the PFT laboratory of Toronto General Hospital by experienced respiratory technicians. All equipment (ultrasound, fNIRS, and oscillometry) has been applied in the laboratory setting previously. In addition, our research team has expertise in conducting web-based assessments in the participants’ home environment, including IMT, given the COVID-19 environment.

The research coordinator will guide the participants through each step of the study process. Standard operating procedures will be generated for each step related to data collection, data entry, and data handling. The research coordinator will ensure accuracy by periodically auditing the data in our research database. Although the research coordinator will attempt to have the participants complete the entirety of the assessments and questionnaires, if there are unanswered questions or missing data, the data will not be imputed, and analysis will be performed on the available data.

The current institutional and national research ethics guidelines will be followed to ensure data privacy, security, and protection. Participant data will only be accessible by the research study team, and participants will be assigned a random participant ID, which will be linked to all the data. All the study data will be securely stored on a password-protected server. In the event of inappropriate data breaches, the following actions will be undertaken: (1) prevent further breach of information and attempt to retrieve breached information and (2) notify the institutional research ethics board immediately. Further action might be taken according to the recommendations from the research ethics board. Modifications to the study protocol will be approved by the research ethics board before implementation, communicated to funding agencies, and outlined in future publications.

## Results

This research was funded in January 2021, and study enrollment began in August 2021 and will continue until December 2023. As of January 2023, a total of 4 participants with hEDS or G-HSD in the intervention group and 4 participants in the usual care group have completed the study, with 5 other participants with hEDS or G-HSD enrolled. A total of 11 healthy controls have completed the study. The results will be submitted for publication once data collection and assessments are complete.

## Discussion

### Summary

This study will help characterize the multifactorial nature of dyspnea experienced by individuals with hEDS and G-HSD. Given the known impairments in respiratory muscle strength in this population, this study will allow us to assess the synergistic effects of IMT and standard-of-care rehabilitation on dyspnea, PROMs, and exercise capacity, which have not been previously characterized. The findings of this study will inform the feasibility of a larger study using IMT and standard-of-care rehabilitation that will be appropriately powered to assess the effects of IMT on PROMs and clinical outcomes. Furthermore, this study has the potential to inform our understanding of the mechanistic effects that IMT may have on diaphragm structure and function, lung physiology, and neurocognitive adaptations in this population.

The literature describing respiratory manifestations in EDS and G-HSD has generally been limited to a few observational studies and case series involving mainly 4 subtypes: classical EDS, vascular EDS, hEDS, and G-HSD [2,9]. We chose to focus on the population with hEDS, as hEDS comprises the major subtype of EDS, and there is also a study highlighting respiratory muscle weakness and effectiveness of IMT [11]. The population with G-HSD was also chosen, as G-HSD is defined to be on the continuum of EDS and represents one of the most common diagnoses in our GEAR rehabilitation program, and the respiratory sequelae of G-HSD have not been well characterized [3]. Another important consideration factored into our selection of the EDS population was the risk of pneumothorax, which is generally lower in individuals with hEDS and G-HSD than in those with other subtypes. Thus, the inclusion of patients with hEDS and patients with G-HSD is owing to the representation of the majority (>90%) of the patients with EDS followed in our program.

We hypothesize that IMT and standard-of-care rehabilitation will provide a positive synergistic effect on respiratory muscle function, PROMs, and clinical outcomes. IMT has been shown to improve dyspnea by increasing respiratory muscle strength [76]. In addition, aerobic and strength training has been shown to increase the strength of the respiratory and limb muscles and improve oxygen use, ventilatory efficiency, and exercise capacity [20,31]. Furthermore, IMT can have positive effects on dyspnea through neurocognitive adaptations [77]. Breathing exercises may induce motor-sensory neural adaptations in the diaphragmatic and respiratory muscles, which can improve dyspnea tolerance [77]. It is also postulated that improvements in exercise capacity and dyspnea levels through IMT may result in greater independence in daily activities and improved HRQL [78]. Despite the proposed beneficial effects of IMT, the ideal duration remains to be determined, with 8 weeks chosen for this study based on the recommendation that a duration of at least 6 weeks is required to derive respiratory muscle adaptations [79-81].

Owing to the COVID-19 environment, a large proportion of research assessments and in-person care visits have transitioned to a web-based environment [82,83]. Patients often express concerns about the possibility of COVID-19 exposure and travel expenses for in-person assessments. Furthermore, the GEAR program has also adapted its format, with a proportion of web-based training sessions performed. Thus, we are closely monitoring enrollment numbers and if recruitment proves to be challenging because of the requirement for in-person visits, we will be able to amend the protocol to allow assessments to be performed via the web. In fact, most of the assessments in this study can be administered via the web, including all PROMs, respiratory muscle endurance testing, and IMT with electronic tracking on the device itself. The results of this study will demonstrate the potential of performing web-based IMT, especially with the emergence of tele-rehabilitation programs.

### Limitations

This study has several limitations that need to be highlighted. First, our study focuses on hEDS and G-HSD, which represent most EDS disorders in our program. However, the findings may not be generalizable across less prevalent EDS subtypes (eg, classic EDS or vascular EDS). Second, all participants in this RCT will be enrolled in the GEAR program, and we anticipate that any differences in training volumes or physical activity levels will be negligible between the groups after randomization, but any differences over the 8-week IMT program will be explored. Third, we are unable to monitor adherence to the GEAR program in the intervention group. Moreover, IMT may not be suitable for all participants because of time restrictions, training preferences, and work-school schedules. However, the web-based environment provides participants with the flexibility to uptake the IMT program that best suits their schedules.

### Conclusions

This study aims to provide a better understanding of the contributors to dyspnea in hEDS or G-HSD and highlight the association between dyspnea and respiratory muscle function, PROMs, and exercise capacity. The combination of IMT and standard-of-care rehabilitation training may provide a novel therapeutic strategy to improve respiratory muscle function and PROMs. A better understanding of the feasibility and efficacy of IMT and standard-of-care rehabilitation will provide insight into the use of IMT in the population with EDS and the population with G-HSD, given a shift toward tele-rehabilitation programs in the COVID-19 environment. This research will pave the way for future studies to evaluate respiratory management strategies in this population.

## Appendix

Multimedia Appendix 1 Peer review report from the 2020 GoodHope Ehlers-Danlos Syndrome Foundation grant competition.

## Abbreviations

CONSORT: Consolidated Standards of Reporting Trials
COPD: chronic obstructive pulmonary disease
CPET: cardiopulmonary exercise test
EDS: Ehlers-Danlos Syndrome
fNIRS: functional near-infrared spectroscopy
GEAR: GoodHope Exercise and Rehabilitation Program
G-HSD: generalized hypermobility spectrum disorder
hEDS: hypermobile Ehlers-Danlos Syndrome
HR: heart rate
HRQL: health-related quality of life
IMT: inspiratory muscle training
MIP: maximal inspiratory pressure
MRC: Medical Research Council
PFC: prefrontal cortex
PFT: pulmonary function test
PROM: patient-reported outcome measure
RCT: randomized controlled trial
T0: baseline
